#### Definition of strategies with missing data

Data available: inclusion of only participants whose criterion considered is filled

Missing=failure: Any missing value will be replaced by the value corresponding to failure

Maximum bias strategy: Strategy comparing the results of two analyzes, one replacing missing data by a failure of the strategy in one group and by a success of the strategy in the other. And inversely in a second time.

## Type I error rate

For the main secondary outcome, the main effect (of the meditation intervention compared to the English intervention) on the global metacognitive composite score will be tested with a two-sided type I error rate  $\alpha=5\%$ ; if significant, the main effect on each of the 3 composite subscores (attentional, constructive and deconstructive) will be tested with a Bonferroni correction ( $\alpha=5/3\%=0.0166\%$ ) to strictly control for type I error inflation.

The evolution of the same scores in the passive control group will be provided for the sake of description.

Each statistical test for the other secondary endpoints will be performed with a two-sided type I error rate  $\alpha=5\%$ .

## Descriptive analysis

The frequency and proportion of available data will be described for each variable.

Qualitative variables will be described in terms of number, proportion and exact binomial confidence interval of proportion.

Quantitative variables will be described in terms of absolute frequency, mean, standard deviation, confidence interval of the mean, median, interquartile range, minimum, and maximum.

Descriptive analysis will be performed overall and by intervention group.

## Comparative/Correlational analysis

Qualitative variables will be compared between the groups with the  $\chi^2$  test or the corrected  $\chi^2$  or non-parametric Fisher's exact test, according to the values of expected frequency under the independence assumption. A logistic or polytomic model will be used to consider adjustments if necessary. The assumption of log-linearity of the association will be systematically checked.

Quantitative variables will be compared between 2 groups of intervention by Student t test if the conditions of validity are respected (normal distribution, homogeneous variances). If the variances are unequal between the 2 groups, a t-test for unequal variances will be used, if the distribution is not normal, a non-parametric Wilcoxon test will be used.

Quantitative variables will be compared between 3 groups of intervention with analysis of variance (ANOVA) if the conditions of validity are respected (normal distribution, homogeneous variances). If the distribution is not normal, a non-parametric Kruskal-Wallis test will be used.

Covariates will be added to the model, or linear regression model will be used to adjust on variables, if necessary. The assumption of linearity of the association will be systematically checked. The other assumptions of the model (normality and homoscedasticity of residuals) will be studied. A transformation of the quantitative variable may be considered if necessary.

Multiple regression models, general linear models and/or independent component analyses, principal component analyses or confirmatory factor analyses would be performed to assess the relationships between variables and/or to extract components from multiple variables,

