#### Study on the expert meditators:

Studies of expert meditators assessing meditation-related changes in brain activity have shown an effect size of  $d=0.74$  (calculated for fMRI change in the insula in response to emotional stimuli; Lutz et al., 2013).

For reasons of recruitment capacity, it was agreed to recruit 30 expert meditators into the trial.

The inclusion of 30 expert meditating participants will allow us to have a power of 95% for the comparison to the 126 non-expert participants, with a first species risk of 5%, to show an effect size of 0.74 in the comparison of brain imaging data.

For the comparison of the 30 expert participants to the 126 non-expert participants, we will have 90% power to show an effect size of 0.67 and 80% power to show an effect size of 0.58, with a two-sided first species risk of 5%.

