## Sample size

### **For the randomized clinical trial with non-expert seniors:**

The comparison of the meditation vs. no intervention arms will focus on the change in 1) volume and 2) metabolism of the anterior cingulate cortex from baseline to the end of the 18-months intervention, with an expected effect size of 0.75.

We expect the same effect size of 0.75 for the comparison between the meditation arm and learning of English arm on the change in 1) volume and 2) metabolism of the insula from baseline to the end of the 18-months intervention.

To demonstrate an effect size of 0.75 for each of the four comparisons, with 80% power and a two-sided type I error of 1.25% (Bonferroni correction for test multiplicity), 42 participants per arm need to be included for a total of 126 participants.

In order to increase the statistical power of the secondary analysis on the PET-FDG examination carried out starting from the second wave of inclusion, 24 additional participants will be recruited (additional 8 participants per group) for a total of 150 participants.

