### **Experienced meditators:**

For recruitment capacity reasons, it is possible to recruit 30 experienced meditators in the study. With the inclusion of 30 experienced meditators and 126 non-expert seniors, our power to highlight an effect size of 0.74 in the comparison of brain imaging data with a significance level of 5%, is 95%.

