### **Objective 4 (WP 1 to 6)**

All cognitive measures, psychoaffective measures, life factors, blood, sleep and imaging measures at inclusion will be compared between the group of expert in meditation and the non-expert seniors. (see Section “*Descriptive analysis*” above for comparative methods)

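### In the 30-versus-126 expert comparison, choosing Student or Welch from the observed variances lets unadjusted tests of normal measures drift from 5% to about 6.7% or 3.9% if the SDs differ modestly; specifying Welch removes this

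*Combined protocol and SAP*

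**What the plan says.** The Comparative/Correlational analysis section of the secondary SAP makes Student's t the default for two groups, provided the data look normal with homogeneous variances. It then adds: "If the variances are unequal between the 2 groups, a t-test for unequal variances will be used". Non-normal variables go to Wilcoxon. No variance test and no threshold for calling variances unequal is named.

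Under Objective 4, measures "at inclusion will be compared between the group of expert in meditation and the non-expert seniors". For the methods, Objective 4 points to the Descriptive analysis section. That section contains no comparative tests, and the only general text on comparative methods is the section that follows it, quoted above.

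The sizes come from the Experienced meditators paragraph: "With the inclusion of 30 experienced meditators and 126 non-expert seniors". The Sample size section later enlarges the senior group: "24 additional participants will be recruited (additional 8 participants per group) for a total of 150 participants". On the error rate, the Type I error rate section says: "Each statistical test for the other secondary endpoints will be performed with a two-sided type I error rate", set at 5%.

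**The concern.** Student's t pools the two variances. With equal groups this does almost no harm when the SDs differ. At 30 against 126 or 150, the larger group dominates the pooled variance while the smaller group dominates the true variance of the difference. If the experts vary more than the seniors, the standard error is too small and the test rejects too often; if they vary less, it is too large and power is lost.

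A preliminary look at the variances is meant to guard against this. With 30 in one group it misses a modest SD difference most of the time, and Student's t is then kept where it does not hold its level. Equal SDs are not guaranteed by design: experts need at least 10,000 hours of practice and come through Buddhist centres on teachers' recommendation, while seniors come from a local public campaign (protocol 4.2.1 and 4.3). At stake is whether 5% means 5% for the Objective 4 measures tested this way.

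**Working it through.** **Inputs from the documents.** n1 = 30 experts; n2 = 126 seniors, or 150 after the enlargement; two-sided 5%; Student by default, Welch if the variances look unequal.

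**Inputs assumed.** The SD ratio r (experts/seniors) is not given; it was varied from 0.5 to 2.0, and 0.8 to 1.3 is taken as modest. The check is taken as a two-sided F test on the variances at 5%, with 1% and 10% and a Brown-Forsythe check as alternatives. Data are normal.

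**Step 1: the plan's own power figures.** Power ≈ Φ(d / √(1/n1 + 1/n2) − 1.96), with √(1/30 + 1/126) = √0.04127 = 0.2031.

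- d = 0.74: 0.74/0.2031 − 1.96 = 1.68, power 95.4% (95.2% with the noncentral t). The secondary SAP states 95%.
- d = 0.67: 91.0% (90.6%). d = 0.58: 81.5% (81.0%). Protocol 11.2 states that "we will have 90% power to show an effect size of 0.67 and 80% power to show an effect size of 0.58".

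The stated figures reproduce.

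**Step 2: why Student's t drifts.** Put the senior SD at 1. The true variance of the difference is r²/30 + 1/126. Student's t estimates, on average, [(29r² + 125)/154] × (1/30 + 1/126).

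- r = 1.2: true 0.0480 + 0.0079 = 0.0559; estimated (166.76/154) × 0.04127 = 0.0447. The standard error is too small by a factor √(0.0559/0.0447) = 1.12.
- r = 0.8: true 0.0213 + 0.0079 = 0.0293; estimated (143.56/154) × 0.04127 = 0.0385. The true standard error is √(0.0293/0.0385) = 0.87 of the one used.

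**Step 3: the two-step rule.** The check and the t statistic use the same sample variances, so the rule was simulated directly: 400,000 null trials per row, Monte Carlo standard error about 0.04 points, 30 vs 126.

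| r | Student alone | Welch alone | Check finds unequal variances | Two-step rule |
|---|---|---|---|---|
| 0.80 | 2.5% | 5.1% | 29% | 4.0% |
| 0.90 | 3.6% | 5.0% | 10% | 4.1% |
| 1.00 | 5.0% | 5.0% | 5% | 5.1% |
| 1.10 | 6.5% | 5.0% | 11% | 6.1% |
| 1.20 | 8.0% | 5.0% | 27% | 6.6% |
| 1.30 | 9.5% | 5.1% | 47% | 6.7% |
| 1.50 | 12.3% | 5.0% | 81% | 5.9% |
| 2.00 | 18.4% | 5.0% | over 99% | 5.1% |

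A run of 1,000,000 trials gave 3.9% at r = 0.8 and 6.6% at r = 1.2 to 1.3. With 150 seniors it gave 6.7 to 6.8% at 1.2 to 1.3 and 3.9% at 0.8.

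**Step 4: sensitivity to the unstated check (30 vs 126).** A 10% F check gives 6.2% at r = 1.2 and 4.3% at 0.8. A 1% F check reaches 7.8% at its worst and 3.2% at its lowest. Brown-Forsythe at 5% ranges from 3.8% to 7.2%.

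**Step 5: equal arms.** With 42/42 or 50/50 the two-step rule stays between 4.9% and 5.1% at every ratio tried.

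**Step 6: power.** At r = 0.8 and a difference of 0.5 senior SDs, the two-step rule has 78% power and Welch 82%. With equal SDs and d = 0.74, Student has 95.1% and Welch 94.5%, a difference of 0.6 points.

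**Step 7: robust standard errors.** In the two-group case without covariates, 30 vs 126, t reference with 154 df: HC0 rejects 5.8% and HC1 5.6% with equal SDs, and 5.8% and 5.7% at r = 1.2. HC3 stays at 5.1 to 5.2%.

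**The case against.** **The numbers rest on assumptions.** The plan gives no SDs, test or threshold. This stands. A reader might infer that the rule simply pushes the test to nearly 7%, or below 4%. The documents do not support that as a fact: with equal SDs the rule is at 5.1%, by a ratio of 2.0 it is back to 5.1%, and with a 10% check 4% is not breached. The direction is open too. Strict selection could narrow the experts' spread, which makes the test conservative, and both groups share the age, education, cognitive and most health criteria.

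**Much of Objective 4 does not use this rule.** This also stands. Protocol 11.3.6 says secondary analyses will be adjusted for confounders, which means covariates or linear regression. Voxel-wise imaging runs in SPM and the attentional fMRI task preferentially in PLS. Non-normal variables go to Wilcoxon and categorical ones to chi-square or Fisher. A reader might infer that every expert-senior test is affected, but only unadjusted comparisons of normal scalar measures are. The 30-versus-126 power statement itself concerns brain imaging data.

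**The rule is worded for intervention groups, which experts are not.** True. Its use here is an inference from Objective 4's pointer, though no other general comparative-methods text is available to point to.

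**The effect is minor beside multiplicity and confounding.** Protocol 2.2.2 lists Objective 4 among the more exploratory objectives; it is non-randomised and covers many measures, each at an uncorrected 5%. That limits the importance of the point without making the rule correct.

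**Conclusion.** The point holds within those limits. For unadjusted comparisons of normally distributed scalar measures between 30 experts and 126 to 150 seniors, and assuming an F check at 5%, the actual level is about 6.6 to 6.8% if the experts' SD is 20 to 30% larger and about 3.9% if it is 20% smaller. A 10% check brings these to about 6.2% (SD 20% larger) and 4.3% (20% smaller). Because the plan fixes no threshold, the true level is not pre-specified.

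The source of the drift is keeping Student's t with unequal group sizes. The preliminary check reduces it (8.0% to 6.6% at r = 1.2) but does not remove it, and the drift fades once the SDs differ by half or more. Welch alone holds 5% at every ratio from 0.5 to 2.0.

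A reader might extend this to the randomised comparisons, since section 2.3 of the primary SAP has the same wording. Step 5 shows it does no harm with equal arms, so neither the primary outcomes nor the main secondary outcome is affected. The Wilcoxon branch after a normality check was not simulated. This is an optional improvement of low severity.

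**What to change.** Add to Objective 4 of the secondary SAP: unadjusted two-group comparisons of quantitative variables between experts and non-expert seniors use the unequal-variance (Welch) t-test, with no preliminary variance check; when covariates are included, use a linear model with HC3-type small-sample robust standard errors. The type has to be named, because HC0 or HC1 would reject 5.6 to 5.8% even with equal SDs, where the present rule gives 5.1%. Correct Objective 4's methods pointer at the same time, so that it names the comparative section.

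Cost: a sentence or two of text, and about 0.6 points of power at d = 0.74 if the SDs are equal (94.5% instead of 95.1%). That figure is for the unadjusted Welch test only. No change is needed for the randomised arms.

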## Analysis of imaging data

For voxel-wise analyses, MRI and PET data will be processed and analyzed using Statistical Parametric Mapping software (Wellcome Trust Centre for Neuroimaging, London, United Kingdom). T1-weighted MRI images will be segmented, spatially normalized to the MNI space, modulated to correct for nonlinear warping effects using the Voxel-Based Morphometry toolbox and smoothed. PET images will be co-registered onto corresponding MRI, normalized using the deformation parameters defined from the VBM procedure performed on the corresponding MRI, scaled using the mean PET value of the cerebellar gray matter and smoothed. Quality control for raw data and for each step of data processing will be performed by experts. PET data will be corrected for partial volume effects (PVE, PMOD Technologies) using a 2-tissue compartment model and analyses will be repeated with PVE-corrected PET data whenever required. Statistical analyses will include group comparisons (with ANOVA) and correlations (regression analyses) with SPM. For T1-MRI, the freesurfer software will also be used for complementary analyses on cortical thickness. Analyses will include age, MMSE, sex and education as covariates when required. Other possible covariates (risk factors for AD, cardiovascular risk factors, neuroticism) will be included according to analyses.

For resting-state fMRI data, data will be processed as described in La Joie et al. (2014), including slice timing correction, realignment to the first volume, spatial normalization, smoothing, masking to include only gray matter voxels and exclude the cerebellum (based on the T1-weighted and non EPI-T2\* volumes) and temporal band pass filtering (0.01–0.08 Hz). Analyses will include seed-based functional connectivity analyses and independent component analyses (see Mevel et al., 2013; La Joie et al., 2014; Arenaza-Urquijo, 2015).

For fMRI data acquired during attentional and emotional tasks, preprocessing steps (including slice timing correction, realignment to the first volume, spatial normalization and smoothing) will be performed using Statistical Parametric Mapping software (Wellcome Trust Centre for Neuroimaging, London, United Kingdom). Statistical analyses will include comparison of brain activity between various task conditions for the different groups using ANOVAs and regression analyses. Due to task specificities, these analyses will be preferentially performed with a multivariate (PLS) technique for the attentional task and an univariate (SPM) technique for the emotional task. Analyses will include age, MMSE, sex and education as covariates when required. Other possible covariates (risk factors for AD, cardiovascular risk factors, neuroticism) will be included according to analyses. Based on these results, supplementary analyses will be performed to determine brain areas common to the attentional and emotional tasks in each group.

## Calculation conventions for statistical analysis

### Conventions for time calculations

- Time between 2 dates **in months**  $= \frac{(\text{Date 2} - \text{Date 1})}{30.4375}$
- Time between 2 dates **in years** will be estimated as the number of years between two dates. The function "YRDIF" of SAS will be used with the "Actual" option.

Convention for dates: Except in special cases, if the day is missing, the convention is to use the value "15", i.e. mid-month. If the day and month are missing, the convention is to use the value "1" for days and the value "7" for month, i.e. mid-year. This convention allows us to measure time estimates. The biostatistician makes these imputations at the time of analysis and consistency is checked at the time of data review.

### Conventions for the calculation of the change (delta) of measurement between 2 visits

The difference between two measurements, one taken at D00 and a second taken at a visit posterior to D00 (follow-up visit DXX) will be calculated using the following formula:

- Delta = (measurement at DXX – measurement at D00)

### Conventions for BMI calculations

- $BMI = \frac{Weight(kg)}{Height^2(m)}$

### Conventions for handling missing data

The following values are used in the database to describe the missing data:

- « NK » or « K »: Unknown
- « ND » or « D »: Not done
- « NA » or « A »: Not applicable

There will be no distinction in the statistical analyses according to the type of missing data.

## Software used

The analyses will be performed using Statistica, Matlab/SPM and R softwares (last version or otherwise indicated); other softwares might be used and this will be indicated in the corresponding article.

# Analysis plan

---

## Participants characteristics

The following characteristics are described for all enrolled participants overall and per group.

### At enrolment

- Socio-demographic characteristics
  - Gender
  - Age (years)
  - Level of education (in number of years from the 1st year of school = CP in France)
  - Number of years in retirement
  - Memory Complaint (score at MacNair)
  - Familial history of AD (percentage yes)
- Clinical characteristics
  - Diastolic and systolic blood pressure (mmHg)
  - Height (m), weight (kg) and BMI (in kg/m^2, in classes)
  - Hip and waist circumferences (cm)
- Diagnostic battery test
  - Laterality-Edinburgh
  - MMSE
  - MADRS
  - Grober and Buschke
  - Short Version Winsconsin
  - English test
- For expert meditators,
  - Total number of hours in life practicing formal meditation
  - Total number of hours in life practicing formal meditation in retreats
  - Total number of daily meditation hours in life
  - Frequency of daily practice (days per week)
  - Total number of meditation hours in life in practices related to
    - compassion and loving-kindness meditation
    - concentration related meditations
    - mindfulness/wisdom related meditations
    - in ritual-related practices (chanting, puja,...)

### At the end of the trial

- Death

- Compliance
  - Total number of formal home practice sessions and hours of
    - Total number of classes attended
    - Total number of reported practice sessions
    - Total number of minutes of formal practice
- Total number of minutes of informal practice Adverse events
  - Severity
  - Relationship to the study intervention or radiopharmaceutical drugs

### Partners' characteristics

- Socio-demographic characteristics
  - Gender
  - Age (years)
  - Relationship to participant
  - Live with participant (Yes/No)
  - Number of years knowing the participant
  - Number of hours per week spent with the participant

### Analysis of trial objectives

#### Primary objectives (Objectives 1 and 1bis)

See the attached SAP document for primary objectives

#### Secondary objectives

##### *Objective 2 (WP 1 to 6)*

For the main secondary outcome, the difference between the inclusion and 18 months of i) the global metacognitive composite score, and ii) the attentional, constructive and deconstructive subscores, will be compared between the meditation intervention and language learning intervention groups.

These scores will be computed as described in (Schlosser et al., Submitted). Briefly, the metacognitive composite score drew from the following self-report measures employed in the Age-Well randomised controlled trial (See Poisnel et al. for details and corresponding references): the Compassionate Love Scale (CLS; stranger-humanity version), the Drexel Defusion Scale (DDS), the Five Facet Mindfulness Questionnaire (FFMQ), the Interpersonal Reactivity Index (IRI), the Multidimensional Assessment of Interoceptive Awareness Version 2 (MAIA-2), and the Prosocialness Scale. Amongst those, seven subscales were judged to primarily capture attentional aspects: noticing (MAIA subscale), attention regulation (MAIA), emotional awareness (MAIA), self-regulation (MAIA), body listening (MAIA), observing (FFMQ), and acting with awareness (FFMQ). Four (sub)scales were judged to primarily capture constructive aspects: the CLS, empathic concern (IRI subscale), perspective taking (IRI), and the Prosocialness Scale. Another four scales were judged to primarily capture deconstructive aspects: the DDS, non-judging (FFMQ), non-reactivity (FFMQ), distress (IRI).

To compute each composite score, scale scores will be first standardised using their baseline mean and standard deviation, and the sum of the standardised scale scores will then be divided by the number of scales included in the respective composite. Scales will be reverse-scored if higher total scores reflect worse functioning. Ergo, higher composite scores will indicate higher capacities in the psychological processes characterising the three meditation families. Participants with missing scale scores will not be included in the composite score to which this scale is assigned.

The evolution of the same scores in the passive control group will be provided for the sake of description. Moreover, the difference between the inclusion and 18 months of all additional composite scores and individual behavioural cognitive, psychoaffectives, life, blood, sleep and imaging measures will be compared between

the three groups. (see Section “*Descriptive analysis*” above for comparative methods). Mixed models will be used to evaluate the evolution from baseline to M18, taking into account observations of M9. Analyses of the effect of the exposure to meditation/English learning (number of hours of practice, number of sessions...) will also be performed.

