| Compassion, support, meditation | Trait Mindfulness: Five-Facet Mindfulness Questionnaire (FFMQ-15)** | AHQ          | Multiple           | Baer et al. 2012                                                                                           | x                 | x                  | x           | x            | X                              | - Autoquestionnaire
- At home
- On computer or paper *       |
|                                 | Drexel Defusion scale                                               | AHQ          | Unique             | Forman, 2012                                                                                               | x                 | x                  | x           | x            | X                              | - Autoquestionnaire
- At home
- On computer or paper *       |
|                                 | Multidimensional Assessment of Interoceptive Awareness (MAIA)       | AHQ          | Multiple           | Mehling et al. (2012)                                                                                      | x                 | x                  | x           | x            | X                              | - Autoquestionnaire
- At home
- On computer or paper *       |
|                                 | Depression Death Scale Revised (21 items)                           | AOS          | Multiple           | Templer et al., 2012                                                                                       | x                 | x                  |             | x            | X                              | - Autoquestionnaire
- At the center
- On computer or paper * |
|                                 | Self-compassion-short version                                       | AHQ          | Unique             | Raes et al., 2011, adapté de Neff, 2003                                                                    | x                 | x                  | x           | x            | X                              | - Autoquestionnaire
- At home
- On computer or paper *       |

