|                                 | Other Compassion **                                                 | AHQ          | Unique             | Pommier, 2011                                                                                              | x                 | x                  | x           | x            | X                              | - Autoquestionnaire
- At home
- On computer or paper *       |

|                  |                                               |         |                 |                                                                                |   |   |   |   |   |                                                                    |
|------------------|-----------------------------------------------|---------|-----------------|--------------------------------------------------------------------------------|---|---|---|---|---|--------------------------------------------------------------------|
|                  | The COPE index**                       | AHQ     | Multiple        | McKee et al. 2003                                                              | x | x | x | x | X | - Autoquestionnaire
- At home
- On computer or paper *       |
|                  | MOS Social Support Survey**            | AHQ     | Multiple        | Sherbourne & Steward 1991                                                      | x | x | x | x | X | - Autoquestionnaire
- At home
- On computer or paper *       |
|                  | Prosocialness scale **                 | AOS     | Unique          | Caprara et al., 2005                                                           | x | x | x | x | X | - Autoquestionnaire
- At the center
- On computer or paper * |
| Emotion   | Penn State Worry Questionnaire - short | AHQ     | Unique          | Meyer et al 1990                                                               | x | x | x | x | X | - Autoquestionnaire
- At home
- On computer or paper *       |
|                  | Emotion regulation abilities           | AHQ     | Multiple        | Gross & John, 2003                                                             | x | x | x | x | X | - Autoquestionnaire
- At home
- On computer or paper *       |

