### **Secondary outcomes**

#### **Behavioral outcomes (OBJECTIVES 2, 4, 6, 7 and 9):**

The main behavioural outcome will correspond to the comparison between meditation intervention and language learning intervention on the global metacognitive composite score, consisting in the mean of the attentional, constructive and deconstructive subscores as defined in (Dahl et al., 2015) and updated in (Schlosser et al., Submitted); see Section “*Analysis of trial objectives*” below for further details about this score.

Additional composite scores will be computed as z-scores measured from the neuropsychological tests and/or the questionnaires. Composite scores will correspond to the mean of z-scores calculated from all the cognitive scores obtained for the corresponding cognitive function that will have a normal distribution and will not have floor or ceiling effect. Additional exploratory analyses will be conducted on all individual behavioural measures obtained.

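### The main secondary composite drops a participant for one missing scale, in conflict with the same SAP's intention-to-treat rule; two instrument names also need confirming

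*Combined protocol and SAP*

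**What the plan says.** The secondary SAP (Behavioral outcomes) makes the comparison of meditation with English learning on a global metacognitive composite the main behavioural outcome. It defines that score as "consisting in the mean of the attentional, constructive and deconstructive subscores". Under Type I error rate, the global score is tested at a two-sided 5%. The three subscores follow, with a Bonferroni correction, only if it is significant. Every other secondary endpoint is simply tested at 5%.

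Under Objective 2 the SAP names six source questionnaires, among them "the Compassionate Love Scale (CLS; stranger-humanity version", and assigns their scales to the subscores. For one subscore it states: "Four (sub)scales were judged to primarily capture constructive aspects: the CLS, empathic concern (IRI subscale), perspective taking (IRI), and the Prosocialness Scale". It then gives the missing-data rule: "Participants with missing scale scores will not be included in the composite score to which this scale is assigned".

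The section Definition of analysis populations in the same SAP includes all randomised participants in their allocated groups and fills missing values with failure. It leaves the choice among its analysis strategies to the principal investigator, with validation by the executive committee.

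Objective 2 names "the Multidimensional Assessment of Interoceptive Awareness Version 2 (MAIA-2" as a source. Protocol Table 6 lists "Multidimensional Assessment of Interoceptive Awareness (MAIA" with a 2012 reference and no version number. Its nearest entry to the love scale is "Other Compassion".

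**The concern.** Two rules cover the same score and give different analysis sets: one removes people, the other keeps everyone. Nothing says which governs this outcome, and the strategy can be chosen later. This is the one secondary outcome with a stated testing sequence, and the sequence starts with the global score, which has the most ways to be incomplete. If participants are dropped after randomisation, the comparison is no longer of the groups as randomised, and power falls. If they are kept by assigning failure to the whole composite, nearly complete records are overwritten with an extreme value.

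The instrument names matter for the same reason. The love scale is one of four constructive components, and MAIA supplies five of the seven attentional ones, so the instrument and version used determine what is measured.

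**Working it through.** **1. Structure (secondary SAP, Objective 2).**

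| Score | Component scales | Questionnaires |
|---|---|---|
| Attentional | 5 MAIA + 2 FFMQ = 7 | 2 |
| Constructive | CLS + 2 IRI + Prosocialness = 4 | 3 |
| Deconstructive | Drexel Defusion + 2 FFMQ + 1 IRI = 4 | 3 |
| Global | 7 + 4 + 4 = 15 | 6 distinct |

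The outcome is the change from inclusion (V1) to 18 months (V3), so a full record holds 2 × 15 = 30 component values.

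**2. The two rules applied to one case.** Take a participant whose only gap is the Prosocialness Scale at V3: 29 of 30 values are in hand.

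- Objective 2 rule: no constructive score at V3, so no constructive change. The global score is the mean of three subscores, so no global change either. The SAP does not spell out this last step; it follows from the definition.
- Intention-to-treat rule: the participant must be analysed.
- If the Objective 2 rule is final, the participant is excluded and the intention-to-treat rule is not met.
- If it only leaves the score blank, missing = failure then fills the whole composite. For its sensitivity analysis the same section equates failure with the minimum observed difference across all groups. On that reading, 29 observed values give way to the worst change seen in the trial.

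**3. Illustrative size.** The plan gives no missingness rate, sample size or power for this composite, so there is no figure of its own to reproduce. Assume a missing rate m per questionnaire per visit, independent, with q questionnaires at two visits:

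share lost = 1 − (1 − m)^(2q)

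| m | Attentional (q = 2) | Constructive or deconstructive (q = 3) | Global (q = 6) |
|---|---|---|---|
| 1% | 3.9% | 5.9% | 11.4% |
| 2% | 7.8% | 11.4% | 21.5% |

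For the global score: 1 − 0.99^12 = 0.114 and 1 − 0.98^12 = 0.215.

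If all six questionnaires go missing together, the loss is 1 − (1 − m)^2: 2.0% at m = 1%, 4.0% at 2% and 9.8% at 5%.

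**4. Effect on precision.** The lockdown annex counts 135 seniors; with 1:1:1 allocation that is 135 / 3 = 45 per arm. Retained under independence: 45 × 0.886 = 39.9 at m = 1%, and 45 × 0.785 = 35.3 at m = 2%. The standardised difference detectable with 80% power at a two-sided 5% (noncentral t) is 0.60 at 45 per arm, 0.63 at 40 and 0.68 at 35.

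**5. Instruments against protocol Tables 5 and 6 (non-expert seniors).**

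- IRI (Table 5), Drexel Defusion and Prosocialness (Table 6): marked at V1 and V3.
- FFMQ: Table 6 lists the 15-item form, marked at V1 and V3.
- MAIA: Table 6, marked at V1 and V3, with no version label.
- Compassionate Love Scale: not named in either table. The compassion entry quoted above is marked at V1 and V3, but nothing links it to this scale.

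Under these names the tables cover 14 of 15 components: attentional 7 of 7 if the listed MAIA is the intended one, constructive 3 of 4, deconstructive 4 of 4.

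**The case against.** The strongest reply is that the drop rule concerns scoring only, and that the intention-to-treat section takes over once a composite is missing. The SAP also defines an available-data strategy and says that the choice depends on the analysis. This weakens the charge of outright contradiction, but it does not rescue the rule. Read in sequence, the two provisions assign failure to a whole score because of one gap, and leaving the choice open means the analysis set is not fixed in advance.

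A second reply is that Objective 2 mentions mixed models using the 9-month data. If they cover this outcome, a participant with one incomplete visit still contributes, and the calculation above overstates the loss. The text does not say whether they do. A visit with a missing scale would still have no composite.

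A third reply is that these questionnaires are largely completed in shared batteries, so missingness probably clusters. That stands, and the percentages are not estimates for this trial.

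A reader might also infer that the composite can be computed for nobody, because a required scale is missing from the schedule. The documents do not support that. The SAP describes all six questionnaires as having been used in the trial. It rests on protocol v9.0 and v10.0, while the tables supplied belong to v12.0. Table 6 often uses short labels. MAIA is scheduled, and the SAP itself tags the five subscales only as MAIA, so that is a version question and not an absent instrument.

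**Conclusion.** The missing-data rule for the main secondary outcome should be changed. Under one reading it excludes randomised participants whom the same SAP says to include; under the other it overwrites a nearly complete record with failure. Using the scales that were observed, or imputing those that were not, is better under either reading.

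The size cannot be fixed from the documents. The 11.4% and 21.5% losses rest on assumed rates of 1% and 2%, on independence, and on needing both visits. They apply to the global score only; the subscores lose less.

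The instrument names are a documentation point to be confirmed. Non-collection of the love scale is not shown. If it were true, only the constructive and global scores would be affected; the attentional and deconstructive subscores do not use that scale.

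**What to change.** Before unblinded analysis:

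1. Replace the drop rule with one stated rule that keeps all randomised participants. One option is the mean of the available standardised scales when at least half of a subscore's scales are present, with multiple imputation otherwise. Another is scale-level multiple imputation throughout. The half-present threshold is a convention and is not taken from the documents.
2. State that this rule overrides missing = failure for this outcome, and keep complete-case as a sensitivity analysis.
3. Say whether the mixed models using 9-month data apply to this outcome.
4. Confirm from the eCRF which compassion scale and which MAIA and FFMQ versions were given at V1 and V3, and use the same names in Table 6 and the SAP. If the love scale was not collected at both visits, redefine the constructive subscore, and through it the global score, explicitly from the scales that were.

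The cost is SAP and table wording, an eCRF check that needs no new data, and a small added assumption for prorated or imputed scores.
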